## **Methods**

## **Design overview**

The study is a two-armed cluster-randomized wait-list controlled trial. Recruitment will be completed between July 2012 and August 2012. Participants are recruited from six communities, which is randomly selected from 24 communities in Pudong district, Shanghai. In order to organize better and reduce potential confounding factors, each community is assigned an unique number for randomization. Using (Predictive Analytics Software, PASW) 18.0 for Windows Random Sampling, six communities are randomized into to either the mutual recovery intervention or wait-list control group. To ensure the effect of the mutual recovery program and take full advantage of the local resources, intervention communities are divided into several subgroups, each containing 15 to 20 participants, based on interpersonal relationships and shared interests, with two prestigious participants as leaders respectively. The intervention group will receive a two-month mutual recovery program intervention, including 7 ninety-minutes, weekly sessions, which are based on a standardized self-designed schedule. Participants in the wait-list group will also receive the intervention one year later. A baseline survey (T1) will be conducted with both the intervention and wait-list control group 6 months before the intervention. The survey will be conducted again right before the intervention began (T2) and immediately after the sessions (T3). Follow-up information will be collected weekly from the subgroup leaders by phone call to record the mental health change process of every participant in mutual recovery program groups

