## **Data collection and Measure**

A baseline survey (T1) will be conducted with both the intervention and wait-list control group 6 months before the intervention. The survey will be conducted again right before the intervention began (T2) and immediately after the sessions (T3). Follow-up information will be collected weekly from the subgroup leaders by phone call to record the mental health change process of every participant in mutual recovery program groups

- **Demographic characteristics**

Including sex, age, marriage status, previous occupation, educational level and so on.

- **Self-reported health**

Height, weight, blood pressure, general health, self-reported chronic disease, smoking, drinking and physical activity.

- **Geriatric Depression Scale-15(GDS-15)**

GDS-15 is used to evaluate depressive risk severity at baseline. GDS-15 contains 15

items to assess depression especially of older adults, using a yes/no answer format. The original GDS have 30 items and the initial validation study indicated high internal consistency, with alpha of 0.94, and high convergent validity, as indicated by a correlation of 0.83 with Hamilton Rating Scale for Depression (HRSD), which suggested a cut-point of 5, with scores of 5 or higher indicative of depression.

- **WHO5 Well-being Index (WHO5)**

WHO5 is used to assess life satisfaction and depression severity. It is initially developed by Bech. P in 1998, then revised and recommended to assess life satisfaction by the psychology research collaboration center of the World Health Organization. It is translated into Chinese and introduced to China in 2004 with acceptable internal consistency and validity. There are 5 items in this scale, using a likert 6 rating format from 0 to 5, and usually the replier would be located as good life satisfaction when scoring over the cut-point of 13.

- **Self-administered Insomnia Questionnaire (SIQ)**

Sleep condition is assessed by Self-administered Insomnia Questionnaire which uses likert 5 rating format, from 1 to 5, and includes 3 items describing 3 aspects of the sleep process, such as: (a) taking a long time to fall asleep; (b) cannot stay asleep; (c) wake up too early. It would be judged as insomnia when any one of the 3 items is positive.

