## **Data analysis**

PASW 18.0 for Windows will be used for data analysis. Pearson Chi-square test will be conducted to compare the two groups on difference of the classified data on 3 assessments. A multivariate ANOVA will be conducted to explore the differences within groups, at each of the 3 testing points, on the measures of sleep, WHO5 and

GDS-15. A series of repeated measures ANOVAs will be conducted to compare the two groups on all the variables tested across the screening, pretesting and post testing assessments. This approach is flexible and it is possible to model the dependence between observations from the same individual. Multilevel models can be applied to normally distributed and non-normally distributed outcomes; we will choose the most appropriate model based on the data.

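### The between-arm comparison is committed to repeated measures ANOVA, which drops anyone missing T2 or T3 on a variable; the multilevel alternative that would keep them is left to a choice made from the data

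*Protocol*

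**What the plan says.** The Data analysis section of the protocol lists four things.

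- Between arms, categorical data: "Pearson Chi-square test will be conducted to compare the two groups on difference of the classified data on 3 assessments".
- Within groups (the third measure being GDS-15): "A multivariate ANOVA will be conducted to explore the differences within groups, at each of the 3 testing points, on the measures of sleep, WHO5".
- Between arms, over time: "A series of repeated measures ANOVAs will be conducted", comparing the two groups on every variable across screening, pretest and post-test.
- An alternative: "Multilevel models can be applied to normally distributed and non-normally distributed outcomes; we will choose the most appropriate model based on the data".

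On timing, the Design overview states: "A baseline survey (T1) will be conducted with both the intervention and wait-list control group 6 months before the intervention". The Data collection and Measure section adds: "The survey will be conducted again right before the intervention began (T2) and immediately after the sessions (T3"). T3 is thus the only survey after treatment. The Abstract gives 237 participants in six communities, 105 in the intervention arm and 132 on the wait-list.

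**The concern.** The repeated measures ANOVAs are the only method the protocol commits to for comparing the arms over time. In the standard form, a person contributes to the analysis of a variable only if that variable was recorded at all three surveys. T2 comes before treatment, so a missed pre-treatment visit discards a post-treatment outcome that was actually collected. Someone seen at T1 and T2 but not at T3 also contributes nothing, although those scores carry information about the missing one.

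Loss is plausible in this design. T1 is six months before a two-month programme, so the surveys span about eight months, in people aged 50 to 80 who screened positive for depression. The arms also face different demands. The intervention arm has seven weekly ninety-minute sessions, homework and weekly follow-up through subgroup leaders. The wait-list arm has none of these during the comparison period, and the Discussion says blinding cannot be used. Retention could therefore differ by arm, and a comparison among completers need not be the comparison that was randomised.

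**Working it through.** The protocol states no attrition rate, power or sample-size calculation, so there is no figure to reproduce beyond 105 + 132 = 237, which agrees. What follows is illustration under stated assumptions.

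**Inputs.** N = 237 (Abstract). T1 is taken as complete. Entry requires a GDS-15 score, so a screening GDS-15 exists for everyone; for the other scales this is an assumption. Let p be the chance of missing each of T2 and T3, assumed to be 5%, 10% or 15%.

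**Participants kept by a standard repeated measures ANOVA.**

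- Same people miss both visits: 237 × (1 − p).
- Misses independent: 237 × (1 − p)².
- Dropped although T3 was observed (independent case only): 237 × p(1 − p).

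| p | Kept, same people | Kept, independent | Lost, independent | Dropped with T3 observed, independent |
|---|---|---|---|---|
| 5% | 237 × 0.95 = 225 | 237 × 0.9025 = 214 | 10% | 237 × 0.0475 = 11 |
| 10% | 237 × 0.90 = 213 | 237 × 0.81 = 192 | 19% | 237 × 0.09 = 21 |
| 15% | 237 × 0.85 = 201 | 237 × 0.7225 = 171 | 28% | 237 × 0.1275 = 30 |

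The two patterns bracket the plausible range. If the same people miss both visits, no observed T3 value is discarded and the loss equals p. A mixed model using all available data keeps all 237 under either pattern, because each has T1.

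**Possible bias.** A simulation of 4,000 trials per setting used arms of 105 and 132, no true effect, and a correlation of 0.6 between visits. Only T3 could be missing. In the intervention arm, missingness depended on the T2 score; in the control arm it did not. Clustering was not simulated.

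| T3 missing, intervention v control | Completers: arm difference at T3 | Completers: T3 minus mean of T1 and T2, between arms | Likelihood-type estimate using all T1 and T2 data |
|---|---|---|---|
| 13% v 10% | −0.07 SD | +0.02 SD | about 0.00 SD on both |
| 24% v 20% | −0.12 SD | +0.04 SD | about 0.00 SD on both |

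The third column is closer to what a repeated measures comparison tests. There the error is small and opposite in sign to the difference at T3. The likelihood-type estimate does well partly by construction, since missingness depended only on observed scores.

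**The case against.** The strongest reply is that the remedy is already in the protocol. The sentences after the ANOVAs describe a flexible approach that models dependence within a person, and then name multilevel models. These can keep people with incomplete series. It follows that deletion is not settled, and a reader who infers that it is goes further than the text. What remains is that the ANOVAs are stated as something that will be done, while the multilevel model is only permitted, with the choice to be made from the data in an unblinded trial.

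A second reply is that missing-data rules and analysis sets commonly sit in a statistical analysis plan, which is not shown. That is right, and their absence from the protocol is not the point here. The point rests on the method the protocol does name.

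Three stronger readings are tempting, and the text does not support them.

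- **The MANOVA also distorts the randomised comparison.** It is described as exploring differences within groups at each testing point. It would drop only people lacking a scale at that survey, and it is not the between-arm test.
- **One missing scale removes a person from everything.** The ANOVAs run variable by variable, so a missing WHO5 affects only the WHO5 analysis. The chi-square comparisons need no complete series at all.
- **Bias is likely because completers are those who benefited.** Nothing in the protocol shows this. The simulated bias depends on assumed missingness, is modest, and changes sign with the contrast.

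**Conclusion.** The point holds in a limited form and should be acted on. The protocol commits the between-arm comparison over T1 to T3 to a method whose standard form drops, for each variable, anyone missing T2 or T3. It permits the better method without committing to it. The firmer harm is lost participants: about 5-15% of 237 if the same people miss both visits, and about 10-28% if misses are independent, at an assumed 5-15% missing per visit. Bias from differing retention is possible; in the settings simulated it was 0.02 to 0.12 SD in size, depending on the contrast. All of these sizes rest on assumed missingness, because the protocol gives none. If attrition proves very low, the practical effect is small, but the model choice would still be open to the data.

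**What to change.** In Data analysis, replace the repeated measures ANOVAs and the choice of model from the data with one prespecified mixed model per outcome:

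- linear for GDS-15 and WHO5, and generalised (for a binary response) for insomnia, which the protocol defines as yes/no;
- every participant with any observed visit included, analysed by the community's assigned arm;
- arm, visit and their interaction as fixed effects, with the arm contrast at T3 named as the comparison of interest;
- random effects for community and for person;
- small-sample degrees of freedom, since six communities in two arms leave only about 6 − 2 = 4 between communities.

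The model assumes that missingness depends only on observed data, and the text should say so.

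No new data are needed. The cost is a wording change, slightly more analysis work, and wider intervals once the community level is included, which reflect the design more honestly. The protocol states that "PASW 18.0 for Windows will be used for data analysis"; the statistician should confirm that this version fits the generalised model and offers the small-sample degrees of freedom, and name other software if it does not.

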## **“Physical and mental pleasure”**

# **Effects of a Mutual Recovery Intervention on Mental Health in Depressed Elderly Community-dwelling Adults: a Pilot Study**

## **Abstract**

**Objective:** To examine the effects of mutual recovery program intervention in older adults with high risk of depression at communities in Shanghai, explore suitable approaches to improve mental health of community elders and provide basis for future policy making.

**Methods/Design:** The study involves a cluster-randomized controlled trial. Recruitment were completed between July 2012 and August 2012. Using a, we randomize 6 communities (N=237) into either the intervention group (3 communities, n=105) or to a wait-list control group (3 communities, n=132). All participants should meet screening criteria of depression, which is defined by The Geriatric Depression Scale (GDS-15). From March 2013 to May 2013, participants in the intervention group will receive a two-month mutual recovery program intervention, including 7 ninety-minutes, weekly sessions, which are based on a standardized self-designed schedule.

**Discussion:** Mutual recovery is a comprehensive and inexpensive approach for mental health intervention and could be a creative and helpful strategy to promote the mental health in older adults with high risk of depression at communities.

**Keywords:** Depression; Well-being; Community Intervention; Mental Health; Elderly; Cluster Randomized Trial

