Self-made general demographic questionnaire, including the information of gender, age, marriage, education and pre-work position, is used to control the general study condition and specify the suitable people if this program is going to be generalized in the future.

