## **Discussion**

Mutual recovery is a comprehensive and inexpensive approach for mental health intervention and could be a creative and helpful strategy to promote the mental health in older adults with high risk of depression at communities. Mutual recovery program focused not just only on what to teach participants but also on how to organize and present the information and skills.

The intervention effect may be diluted by participants that are health. Considering the intervention effect, we choose participants that are at high risk of depression. The elderly recruitment for this community-level intervention trial has been successful in identifying a large sample of residents at risk in Shanghai using recruiters drawn from the neighborhoods

During the design of the trial, there are a number of methodological issues that we need to consider. We do not randomize program group and control group by individuals but by communities. Thus, there may be some confounding factors that we cannot control, such as the economy condition, family construction and so on. What's more, blind method cannot be utilized because of the process of community mobilization and publicity. Since we cannot intervene the participants' daily life, participants in the wait-list condition are not hindered in seeking supplementary help while on the wait-list, so there may exist contamination confounding in the control group.

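### The repeated-measures ANOVA across three visits does not isolate the effect at T3, the only post-intervention visit; compare the arms at T3 adjusted for T1 and T2

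*Protocol*

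**What the plan says.** **Timing.** Data collection and Measure places the first survey well ahead of the programme: "A baseline survey (T1) will be conducted with both the intervention and wait-list control group 6 months before the intervention". Design overview gives the other two: "The survey will be conducted again right before the intervention began (T2) and immediately after the sessions (T3"). Both arms are therefore measured twice before any session and once after.

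**Analysis.** The between-arm method in Data analysis is a set of repeated-measures ANOVAs, whose purpose is to "compare the two groups on all the variables tested across the screening, pretesting and post testing assessments". I take screening, pretesting and post testing to be T1, T2 and T3. The section does not say whether the group main effect, the group-by-time interaction or a contrast at T3 is the evidence of efficacy, and it names no baseline covariate. Chi-square tests compare the arms on categorical data at the three assessments, also without adjustment. The section adds that multilevel models can be used and that the model will be chosen on the data.

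**Size.** The Abstract gives six communities and 237 people: 105 in three intervention communities and 132 in three control communities.

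**The concern.** The question is whether the arms differ after the programme, given where they started. A two-arm repeated-measures ANOVA offers two tests that involve arm, and neither answers this directly.

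- The group main effect averages the arm difference over three visits. Two of these cannot show an effect, but they can show chance differences between communities.
- The group-by-time test asks whether the arm difference changes anywhere over the three visits. If the arms drift apart in the six months between T1 and T2, it can reject although the programme did nothing. Drift common to both arms does not matter; it goes into the time effect.

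With three communities per arm, chance differences at T1 and T2 are to be expected. At stake are what the reported result means and, to a lesser degree, power. The scores needed for a direct comparison are already collected in both arms.

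**Working it through.** The protocol states no power, effect size or sample-size calculation, so there is no figure to reproduce. The arm sizes add up: 105 + 132 = 237.

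**Inputs from the protocol (Abstract):** n = 105 and 132, so v0 = 1/105 + 1/132 = 0.01710.

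**Assumptions, none stated in the protocol:** two-sided alpha 0.05; effect d (in SD) at T3 and zero at T1 and T2; equal variances and equal correlation r between visits; no dropout; clustering set aside.

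**Noncentrality of each test:**
- Group main effect: it estimates (0 + 0 + d)/3 = d/3. NCP = (d/3)² / [((1 + 2r)/3) v0], with 1 and 235 df.
- Group-by-time: NCP = (2/3)d² / [(1 − r) v0], with 2 and 470 df.
- Contrast of T3 against the mean of T1 and T2: it estimates d, with variance factor 1.5(1 − r). NCP = d² / [1.5(1 − r) v0], with 1 and 235 df. This equals the interaction NCP, but on 1 df.
- T3 adjusted for T1 and T2 (ANCOVA): it estimates d, with residual variance factor 1 − 2r²/(1 + r). NCP = d² / [that factor × v0], with 1 and 233 df.

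**Example, d = 0.35, r = 0.6:**
- Main effect: 0.01361 / (0.7333 × 0.01710) = 1.09
- Interaction: 0.08167 / (0.4 × 0.01710) = 11.94
- 1-df contrast: 0.1225 / (0.6 × 0.01710) = 11.94
- ANCOVA: 0.1225 / (0.55 × 0.01710) = 13.03

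**Power (%) from the noncentral F:**

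| d | r | Main effect | 2-df interaction | 1-df contrast | ANCOVA | ANCOVA minus 2-df | ANCOVA minus 1-df |
|---|---|---|---|---|---|---|---|
| 0.30 | 0.3 | 18.1 | 50.2 | 60.6 | 69.2 | 19.0 | 8.6 |
| 0.30 | 0.5 | 15.4 | 65.4 | 75.1 | 79.9 | 14.5 | 4.8 |
| 0.30 | 0.7 | 13.6 | 87.2 | 92.6 | 94.0 | 6.7 | 1.4 |
| 0.35 | 0.3 | 22.9 | 64.0 | 73.9 | 81.9 | 17.9 | 8.0 |
| 0.35 | 0.5 | 19.3 | 79.4 | 86.8 | 90.4 | 11.0 | 3.6 |
| 0.35 | 0.6 | 18.0 | 87.9 | 93.1 | 94.9 | 7.0 | 1.8 |
| 0.35 | 0.7 | 16.8 | 95.5 | 97.8 | 98.4 | 2.9 | 0.6 |

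The gap narrows as power nears its ceiling. A simulation of 4000 trials at d = 0.40 and r = 0.5 gave a mean main-effect estimate of 0.137 (0.40/3 = 0.133) and a mean ANCOVA estimate of 0.401. ANCOVA also stayed ahead of both ANOVA tests when the T2–T3 correlation was set 0.15 above the other two.

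**What adjustment leaves behind.** Under equal correlation the T1 and T2 slopes sum to 2r/(1 + r). If the arms differ by a constant amount at all visits, ANCOVA leaves the share 1 − 2r/(1 + r):
- r = 0.6: 1 − 1.2/1.6 = 25%
- r = 0.5: 1 − 1.0/1.5 = 33%

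With a stable difference of 0.3 SD and r = 0.6 that is 0.075 SD; a simulation with no treatment effect returned 0.074. The 1-df contrast returned about zero, because a constant difference cancels.

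**Clustering.** Under no effect (r = 0.5, independent community-by-visit effects), person-level ANCOVA ignoring the six communities rejected in 20% of simulated trials at ICC 0.02 and 34% at ICC 0.05. The interaction test rejected in 30% and 53%. Covariates therefore do not repair clustering, and the power figures above are upper bounds.

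**The case against.** **The main effect is never named.** Data analysis names no term, and group-by-time is the usual efficacy test in a pre/post design. This stands. A reader might infer that the trial's test dilutes the effect threefold and has about 18% power. That holds only if the main effect is the term used, and the text does not settle it.

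**Under the usual reading the loss is modest.** This also stands. A 1-df contrast from the same ANOVA comes within 1 to 9 points of ANCOVA. But the protocol does not name that contrast, and the 2-df test keeps its problem of interpretation whatever its power.

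**Adjustment does not remove imbalance.** Correct: part of a stable community difference remains, and here the contrast does better. That is a reason to report both.

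**Multilevel models are allowed, an SAP may exist, and this is a pilot.** Leaving detail to an SAP is no fault. Here, however, the protocol itself fixes a method across three visits. The multilevel sentence adds no contrast or baseline covariate and leaves the choice to the data. Pilot status lowers the stakes but does not change what the tests estimate.

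**Two further inferences do not hold.** The demographic questionnaire "is used to control the general study condition", while the Discussion says "there may be some confounding factors that we cannot control, such as the economy condition, family construction and so on". A reader might see a contradiction with an analysis that uses no demographic covariate. The first statement promises no covariate model, and the second concerns economic and family conditions. Likewise, the entry rule of GDS-15 at 5 or more would truncate T1 if T1 is the eligibility score, but the documents give no distribution from which to size any inequality of variance.

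**Conclusion.** The concern holds in a limited form and should be fixed. Two of the three assessments precede the intervention, and neither between-arm test of the planned ANOVA isolates the T3 effect. The main effect, if used, estimates one third of it; this is arithmetic and needs no assumption about SD or correlation. The 2-df interaction does not shrink the effect, but it can reject because of arm-specific change before the first session.

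Against T3 adjusted for T1 and T2, the 2-df test loses about 7 to 19 points of power at 0.30 SD and about 3 to 18 points at 0.35 SD, for r from 0.3 to 0.7. The 1-df contrast loses about 1 to 9 points over the same range. Effect size, correlation and alpha are assumptions, and with clustering set aside the figures rank the tests and do not predict the trial's power. The documents do not support the claim that the analysis is invalid or that baseline adjustment would remove all imbalance between communities.

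**What to change.** - In Data analysis, define the efficacy estimate on each scale as the between-arm difference at T3, adjusted for the same scale at T2 and T1, in a model that respects the six communities and uses small-sample degrees of freedom.
- State that neither the across-visit group main effect nor the 2-df group-by-time test alone will be taken as evidence of efficacy.
- Report the 1-df contrast of T3 against the mean of T1 and T2 as a sensitivity analysis, because person-level adjustment leaves part of any stable community difference.
- Show T1 and T2 by arm descriptively, so that divergence before the intervention is visible.
- If T1 is the screening score that determined entry, note that T2 is likely the stronger GDS-15 covariate.

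The cost is a change of wording and a little more analysis. All scores are already collected in both arms.

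### Six communities are randomised, but the between-arm tests take the person as the unit and the plan does not commit to accounting for community clustering

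*Protocol*

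**What the plan says.** The unit of randomisation is clear. Protocol, Design overview: "six communities are randomized into to either the mutual recovery intervention or wait-list control group". The Abstract gives three communities with 105 people in the intervention arm and three with 132 in the wait-list arm. The Discussion repeats the point, "We do not randomize program group and control group by individuals but by communities", but treats it only as a source of uncontrolled confounding.

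The Data analysis section then names three procedures. Pearson chi-square tests compare the groups on categorical data at the three assessments. A multivariate ANOVA explores differences within groups. A series of repeated measures ANOVAs compares the groups across the three assessments. Of this approach it says "it is possible to model the dependence between observations from the same individual". A last sentence says that multilevel models are available for normal and non-normal outcomes and that the model will be picked in the light of the data.

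The section mentions no community term, cluster-robust variance, ICC or small-sample degrees of freedom.

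There is also a second layer in one arm only. Design overview: "intervention communities are divided into several subgroups, each containing 15 to 20 participants, based on interpersonal relationships and shared interests".

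**The concern.** People in the same community tend to be alike, and after a shared programme they may also change alike. A chi-square test or repeated measures ANOVA on individuals counts 237 independent people and so uses about 235 error degrees of freedom for a two-group contrast. The randomised comparison has six units in two arms, hence 6 − 2 = 4.

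The protocol itself gives reason to expect variation between communities. The Discussion names economic conditions and family structure as uncontrolled differences, and mentions community mobilisation. The Intervention section describes sessions held in each community and adapted to each subgroup's needs. So change over time, not only level, may be correlated within a community.

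If it is, a chance difference between two sets of three communities could be reported as an effect of the programme. The Aims section intends the findings to inform policy.

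**Working it through.** **Plan's own figure.** There is none to reproduce: the protocol states no alpha, power, effect size, SD, ICC or sample-size calculation. The counts agree: 105 + 132 = 237.

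**Inputs.** From the Abstract: three communities per arm, so a mean of 105/3 = 35 (intervention) and 132/3 = 44 (control) people per community. Assumed: equal community sizes within each arm, two-sided alpha of 0.05, and a range of ICCs. The ICC that matters is that of the analysed contrast. For group-by-time it is the ICC of the change, because a stable community difference cancels.

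**Formulas.**
- Design effect per arm: DE = 1 + (m − 1) × ICC, with m = 35 and 44.
- Effective N = 105/DE₁ + 132/DE₂.
- Variance ratio R = (DE₁/105 + DE₂/132) / (1/105 + 1/132); SE ratio = √R.
- True size of a nominal 5% person-level test = 2 × [1 − Φ(1.96/√R)].
- Person-level SE = √(1/105 + 1/132) = 0.131 SD. The person-level half-width would be 1.97 × 0.131 = 0.26 SD.
- Half-width with 4 df = 2.776 × 0.131 × √R.

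**Example, ICC 0.01.** DE₁ = 1 + 34 × 0.01 = 1.34 and DE₂ = 1 + 43 × 0.01 = 1.43. R = (1.34/105 + 1.43/132)/0.01710 = 0.02360/0.01710 = 1.380, so √R = 1.175. Size = 2 × [1 − Φ(1.669)] = 9.5%. Half-width = 2.776 × 0.131 × 1.175 = 0.43 SD.

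| ICC | DE₁ / DE₂ | Effective N | √R | True type I error | Half-width, 4 df (SD) |
|---|---|---|---|---|---|
| 0 | 1 / 1 | 237 | 1.000 | 5.0% | 0.36 |
| 0.005 | 1.17 / 1.215 | 198.4 | 1.091 | 7.2% | 0.40 |
| 0.01 | 1.34 / 1.43 | 170.7 | 1.175 | 9.5% | 0.43 |
| 0.02 | 1.68 / 1.86 | 133.5 | 1.327 | 14.0% | 0.48 |
| 0.05 | 2.70 / 3.15 | 80.8 | 1.703 | 25.0% | 0.62 |

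**Simulation of the planned type of test.** There were 4,000 runs per ICC, with three time points, communities of 35 and 44, and community-by-time effects. Rejection rates under no effect were:

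| ICC | Repeated measures ANOVA, group-by-time | Person-level t-test on change | t-test on six community means |
|---|---|---|---|
| 0 | 5.0% | 4.9% | 4.7% |
| 0.01 | 12.5% | 10.6% | 5.5% |
| 0.02 | 17.8% | 14.9% | 5.5% |
| 0.05 | 36.9% | 25.5% | 4.9% |

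The ANOVA is more inflated because its group-by-time test has two numerator degrees of freedom and so takes in the community noise of two time contrasts. The t-test on community means holds its level throughout.

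**Limit of the design.** Three of six communities can be chosen in C(6,3) = 20 ways, so the smallest two-sided p from an exact re-randomisation test is 2/20 = 0.10.

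**The case against.** The best defence is the multilevel sentence. A reader might infer that the plan models only within-person dependence and shuts community out. The text does not support that. The within-person remark is in the preceding sentence, and the multilevel sentence names no level and excludes none, so a model chosen under it could carry community. Random-effect levels are also often settled in a statistical analysis plan, and one may exist. What remains is that the named between-arm tests are firm while the multilevel option is not. A model of visits within persons would satisfy that sentence and still ignore community. This is therefore an analysis fixed badly, not detail left for later.

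Three further limits are fair:
- A reader might infer that the plan reports intervals that are too narrow. It mentions no confidence interval; ±0.26 SD is what a person-level analysis would produce.
- A reader might extend the charge to the multivariate ANOVA. That is described as within groups, so the between-arm point rests on the chi-square tests and repeated measures ANOVAs.
- Inflation is not certain. At ICC 0 there is none, and the wider interval there (0.36 against 0.26 SD) is purely the cost of 4 degrees of freedom. At ICC 0.01 that cost accounts for 0.10 of the 0.17 SD increase.

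The title calls the study a pilot and no formal hypothesis is stated. This softens the consequences, but the stated principal purpose is to examine effects.

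**Conclusion.** Wrong as written. The trial is randomised by community, and the between-arm tests to which the protocol commits ignore community. The multilevel sentence does not cure this, because it binds the analyst to nothing at the community level.

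The size depends on an ICC that the protocol does not give. Over an assumed 0 to 0.05, the true error of a nominal 5% person-level two-sample comparison runs from 5% to 25%. For a repeated measures group-by-time test with community-by-time effects it reaches about 37% at ICC 0.05. The figures assume equal community sizes within arm and leave out any extra correlation from the intervention-arm subgroups. The documents support the statement that a false positive could arise; they do not show that one will.

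**What to change.** In the Data analysis section, replace the person-level between-arm tests with an analysis by randomised community, fixed before the outcome data are examined. Either option will do:

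- A t-test with 4 degrees of freedom on the six community means of the outcome or its change, or on the six community proportions for binary outcomes.
- A mixed model with random community and community-by-time effects and Satterthwaite or Kenward-Roger degrees of freedom (which need not equal 4 exactly).

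Do not use large-sample z-tests or GEE with six clusters. If the mixed model is chosen, state how the intervention-arm subgroups are handled. In the community-means analysis they are nested within community, so their correlation passes into the variation between community means.

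Report the ICC, and present the effect as an estimate with its small-sample interval, in line with the pilot title.

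Cost: a rewritten paragraph, a little more analysis work and wider intervals. No new data are needed. Rewording cannot remove the limit set by having six communities.
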